## CVD markers and vascular function

Plasma lipids and lipoproteins.Serum lipids will be analyzed using a Beckman-Coulter Synchron CX7 (Brea, CA). Serum cholesterol will be assayed by the cholesterol esterase/oxidase/peroxidase method. Triacylglycerols will be measured using the GPO-Trinder method. HDL-C will be measured following precipitation of apoB containing lipoproteins with 50,000 mol wt. dextran sulfate (Sigma Chemical Co.). LDLcholesterol is calculated using the Friedewald equation. The coefficient of variation for these assays is less than 2.0%. Our Clinical Laboratory participates in CDC’s ongoing lipid standardization program.

Blood pressure measurements. Blood pressure measurements will be taken in a quiet room where no other activity is taking place and where temperature fluctuations are minimal. All measurements will be taken on the right arm while the volunteer is seated in the room and allowed to rest for 5 min. before the cuff is wrapped around the arm. Blood pressure will be taken twice by a nurse certified for blood pressure measurements.

Plasma hemostatic factors, inflammatory markers and homocysteine.Factor VII and fibrinogen will be assayed on an Instrumentation Laboratory ACL 3000+ (Lexington, MA). Factor VII activity is assayed by determining the ability of test plasma to correct the clotting time of factor VII-deficient plasma. Factor VII activity is expressed relative to serial dilution of pooled plasma. Fibrinogen will be measured following a standard protocol 166. C-reactive protein, IL-6 and homocysteine will be measured by automated immunoassay with chemiluminescent detection on a DPC-Immulite instrument with reagents supplied by the instrument manufacturer.

Endothelial Function**.** Endothelial function will be estimated by high-resolution ultrasound measurements of changes in brachial artery diameter in response to reactive hyperemia following ischemia (brachial artery flow-mediated dilation) as described by Celemajer et al 167. Prior to each measurement, subjects will rest for 10 min in a supine position. A baseline ultrasound image of the brachial artery will be obtained just proximal to the olecranon process of the elbow. The center of the vessel will be identified when the clearest images of the anterior and posterior walls of the artery are visualized. The transmit zone will be set to the levels of the anterior vessel wall and the depth and gain settings will be optimized to identify the lumen-vessel wall interface. All measurements will be performed with the non-dominant arm with the forearm extended and slightly supinated. Reactive hyperemia will be induced by inflation of a blood pressure cuff to 300-mm Hg for 5 min. The position of the cuff will be approximately 2-3cm distal to the olecranon process. Images of the brachial artery will be obtained 30 seconds prior to inflation (baseline), at the end of each minute during inflation, and continuously for 6 min after cuff deflation. All images will be recorded on super VHS videotape. Vessel diameters will be measured from recordings at 2 different locations relative to an anatomical marker and across 3 cardiac cycles during the diastolic phase.

**Insulin Sensitivity and Secretion**

To determine insulin sensitivity, a frequently sampled intravenous glucose tolerance test (FSIGT) with the addition of exogenous insulin injection will be performed 168. Subjects will be studied after an overnight fast while residing on the metabolic ward (Figure 2). After one hour of rest (RMR measure), 2 IV lines will be placed. Briefly, 300mg/kg glucose is injected at TIME 0, followed by collection of blood samples (4 cc) at 1, 3,4, 5, 6, 7, 8, 10, 12, 14, 16, and 19 min. At TIME=20 min., a bolus of insulin (0.03 U/kg body weight) is given, and frequent sampling resumes at 22, 32, 24, 25, 27, 30, 40, 50, 60, 60, 80, 100, 120, 140, 160 and 180 min. Each blood sample is analyzed for glucose and insulin. These data are then submitted for calculation of the insulin Sensitivity Index (SI), glucose effectiveness (SG), and AIRg using the Minimal Model method of Bergman 169. The minimal model analysis is accomplished using a program developed for a PC (MINMOD-PC, © R. Bergman). Total blood collected during this procedure is less than 150 ml. To date, the clinical staff of the Pennington Center has performed over 250 determinations of insulin sensitivity in lean and obese individuals.

## Neuroendocrine axes

Assessment of diurnal leptin rhythm will be performed using 24-h sampling. GH secretion will be assessed immediately before and during the sleep-induced rise in GH secretion as previously described 170. Cortisol secretion (meal-related increases, and diurnal variation) will be assessed using salivary cortisol concentrations 171,172. This method integrates the minute-to-minute fluctuations in plasma cortisol. The thyroid axis will be measured the following morning after stimulation with TRH 83. The activity of the gonadal axis will be tested by measurement of SHBG, free testosterone and estradiol levels170*.* The experimental protocol for the neuroendocrine axes is shown in figure 3.

Autonomic activity

Spectral analysis of heart rate variability. Autonomic function will be assessed in the fasting state and 30-min. after the ingestion of a meal by spectral analysis of heart rate variability. Subjects will remain in a semi-supine position in a quiet room, while breathing at a controlled rate of 15 breaths/min. They will be instructed to breathe less deeply than normal in order to avoid hyperventilation. Heart rate signals will then be acquired continuously for 5 min. using an ECG lead II, Lifepack 9P (Physio-Control, Redmond,VA), samples at 500 Hz by analogue/digital converter (PCL-812 PC-LabCard, Omega Scientific Company, Stamford,CT). Subjects will then receive a standard meal (Ensure, Abbott Laboratories) containing 40% of RMR measured at baseline of the exercise efficiency test. Heart rate will be measured for the next 30 min. Data will be analyzed by spectral analysis as described by Gao et al 173

24-h urinary norepinephrine excretion*.*24-h urine will be collected while the subjects spend a day in energy balance in the respiratory chamber Norepinephrine excretion rate will be determined as an index of sympathetic nervous activity. It is reproducible in sedentary condition and predicts body weight changes in Pima Indian males 174.

## Muscle/fat biopsy for gene expression

Fat biopsy.After cleansing the skin on the abdomen with povidone-iodine solution, and placing a sterile drape, topical anesthesia is administered with 5mL of a 50% -50% mixture of lidocaine and bupivacaine. A 0.75-cm incision is made in the skin and a 4-6mm Bergstrom needle inserted to collect under aspiration approximately 250-350mg of adipose tissue. The sample is washed in sterile PBS and 75% of it snap frozen in liquid nitrogen, the remaining placed in osmium tetraoxide (potential fat cell morphology). Upon completion of the biopsy, the incision is closed with a sterile bandage, and antibiotic ointment / sterile dressing applied.

Muscle biopsy***.*** A Vastus Lateralis muscle biopsy will be performed using the technique of Bergstrom. After cleansing the skin with povidone-iodine solution, the skin, adipose tissue and skeletal muscle fascia are anesthetized using 5mL of a 50%/50% mixture of bupivicaine and lidocaine (final concentrations 1.0% and 0.125%). The skin is incised (0.75cm) with a #11 scalpel. The fascia fibers are separated with the blunt edge of the scalpel and the Bergstrom needle (4mm) inserted into the vastus lateralis. After suction is applied, approximately 50mg of tissue is cut and removed. Two or 3 passes will be used to obtain at least 200mg of muscle. Pressure is applied and the skin is closed with sterile tape. After cleaning the sample, muscle will be snap frozen in liquid nitrogen. [name] has performed hundreds of these biopsies.

Total RNA extraction and gene expression***.*** RNA will be extracted from individual muscle and subcutaneous fat biopsies containing about 100 mg of tissue, giving yields of 10-20µg total RNA. 50-100mg tissue sample is homogenized in 1mL Tri-Reagent using a glass-Teflon homogenizer. Homogenates are stored for 5 min. at room temperature to permit the complete dissociation of nucleoprotein complexes. RNA is then precipitated, washed and solubilized according to standard techniques.

Two complimentary strategies will be used. *First*, we will use a candidate gene approach, i.e. selecting known genes and measuring gene expression by real-time quantitative fluorescent RT-PCR using the Taqman method. The 49 selected genes are listed in an Appendix. *Second*, expression profiling, will be performed using cDNA microarrays 175-177. This technique allows for simultaneous measurement of thousands of mRNAs by hybridizing small amounts of RNA to multiple DNA sequences spotted onto glass slides. We have purchased an oligo library including more than 19,000 genes.

## Macronutrient Self-Selection and Fat Preference

[name] has developed a macronutrient self-selection paradigm (MSSP©) designed to vary fat content significantly and systematically with sugar, complex carbohydrate, and protein content 107. We have also developed a food preference questionnaire (FPQ©) based on the same design. However, specific foods listed on the FPQ© and those presented for selection/consumption in the MSSP© are mutually exclusive. All foods used in the MSSP© are commercial foods available from the supermarket shelves, and most of the foods in this paradigm are often eaten as snacks. Foods included in the MSSP© require little or no preparation. Other foods that are common sources of fat in the American diet 178 but that require considerable preparation are included on the FPQ©. These instruments have strong test-retest reliability and have been validated with respect to long-term macronutrient intake in men 107 and in women 179. They include foods that are the top sources of fat for Caucasian and minorities in the Delta regions of Louisiana 180.

In the proposed study, the MSSP© will be administered at baseline only. The MSSP© and FPQ© questionnaire will be administered before subjects are put on the AHA diet. The FPQ© will then be administered at 3 and 6 mos. We will test the following hypotheses: 1) Greater preference for and intake of high-fat/high-sugar foods, will be associated with greater difficulty in maintaining CR; 2) Decreasing fat preference scores from baseline is a behavioral adaptation associated with greater success in maintaining CR.

In the final analysis we will investigate the change from baseline for all continuous variables. The analysis will be carried out in two different ways. Using an ANOVA method with treatment groups as fixed effect, we will do a simple analysis of end-of-study change from baseline. The second one is the more detailed and precise analysis using a mixed model approach considering a repeated measures design method with treatment groups and time as fixed effects and subject as random effect. The covariance matrix of the multivariate response for each subject will be modeled appropriately and estimated using the maximum likelihood method. The drop out rates will be compared across all treatment groups (3) testing for equality of proportions using the 2 test. For all analyses, SAS Version 8.1 (or higher) will be used.

| **Table 2**Within subject CV **(%)** | Detectable difference (% from baseline) | n/group | Total N at the end of the study | Power (%) |
| --- | --- | --- | --- | --- |
| Chamber method |  |  |  |  |
| 3 | 5 | 15 | 45 | 80 |
| 3 | 10 | 5 | 15 | 84 |
| 3 | 15 | 3 | 9 | 85 |
| 3 | 20 | 3 | 9 | 98 |
| 5 | 5 | 40 | 120 | 80 |
| 5 | 10 | 11 | 33 | 80 |
| 5 | 15 | 6 | 18 | 85 |
| 5 | 20 | 4 | 12 | 86 |
| Doubly labeled water method |  |  |  |  |
| 7.5 | 10 | 23 | 69 | 80 |
| 7.5 | 15 | 11 | 33 | 81 |
| 7.5 | 20 | 7 | 21 | 83 |

| **RISK / BENEFIT ASSESSMENT** |
| --- |

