## Physical Activity, CR and quality of life

Research unanimously supports the health benefits of PA in humans of all ages 109. It is proposed that increasing PA alone, even in the absence of modifying other health behaviors, will improve quality of life and prevent the onset of chronic disease 110,111. However, to date the only evidence that PA extends the life span is observational in nature 112. It is extremely difficult to determine if increased PA alone decreases mortality because changes in PA are typically associated with changes in body composition and other health-promoting behaviors such as nutrition and smoking cessation, although most studies have adjusted for these potential confounders. Other studies of PA programs without CR have found that increased exercise is generally associated with improved mood, energy, and quality of life. Based upon these findings, we hypothesized that the combination of 12.5% calorie restriction and 12.5% exercise would yield the greatest increases in mood and quality of life and would be associated with the lowest rate of attrition.

| **HYPOTHESES** |
| --- |

Caloric restriction (CR) from birth or during adult life in rodents and lower species prolongs life. Measurement of surrogate markers of longevity suggests that this may be the case in primates as well. The mechanism(s) responsible, and whether this is the case for humans is unknown. CR is associated with several well-known changes in metabolism, including lowering of the metabolic rate. It is unknown which, if any, of these adaptations might be responsible for extending maximum life span. One intriguing hypothesis is that CR lessens the oxidative damage and repair of vital tissues by reducing energy flux and metabolism. CR results in loss of weight and tissues, and lowers the rate of metabolism. A portion of this is the result of the reduced energy intake itself, and another portion is due to the decline in size of the metabolizing mass. Whether there is also a “metabolic adaptation,” defined here as a reduction of metabolic rate that is out of proportion to the decreased size of the respiring mass is a subject of continued debate.

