- **Hypothesis D**. Chronic CR is associated with adaptations in the expression of genes involved in aging, including those related to oxidative stress, energy metabolism (carbohydrate, lipid and protein), and longevity.

**Aims**: Measure for differences in the expression of candidate genes in skeletal muscle and adipose tissue.

- **Hypothesis E**. Psychophysiologic outcomes are improved when the energy deficit is produced by combining PA and CR compared to CR alone.

**Aims** : Measure for differences in weight loss, compliance, rate of drop out, quality of life (QOL), mood, cognitive function, fitness & strength, reaction times, physical activity & food records, and risk of developing an eating disorder.

| **CHARACTERISTICS OF THE SUBJECT POPULATION** |
| --- |

Sixty subjects will be recruited for this study. Only subjects with a 25 ≤ BMI < 30 and 25 ≤ age < 50y for males and 25-45 for females will be included. The lower age limit for females is to avoid the confounding effect of menopause. We will make a conscious effort to enroll 50% males and 50% females. The ethnic/racial composition of the subjects will be proportional to that of Baton Rouge. We expect, therefore, to enroll approximately 20-25% African Americans in the presented study. Female subjects will be checked for pregnancy on a regular basis (each block of testing) and will be discharged from the study if pregnant. The following inclusion/exclusion criteria will also be followed:

Inclusion

- Healthy men and women
- 25 ≤ BMI < 30
- 25 ≤ age < 50 for males
- 25 ≤ age < 45 for females (women age 40-45 will be screened for menopause)

Exclusion

- Personal history of CVD or elevated blood pressure (>160/90 mmHg)
- Personal history of diabetes
- Personal history of major psychiatric disorders
- Personal history of eating disorder
- Post obese (never have had a BMI > 32)
- Smoking
- Subjects exercising regularly (> twice per week)
- Regular use of medications except oral contraceptives
- Individuals with alcoholism or other substance abuse
- Pregnancy or lactation
- Abnormal EKG
- Individuals who have been resident in the greater BTR for < 1y
- Individuals in occupations requiring full alertness and motor skills (airline pilots, etc.) where even a small chance of postural dizziness would be unacceptable

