## Overall Description of the Experiment

The proposed study is a 6 mo. study to be completed over a period of 2 yrs. The study will involve 60 overweight healthy male and female volunteers divided into four equal groups matched for age and gender. As shown in figure 1, the four groups include:

Group 1: Controls (No CR but receiving a healthy diet as per the American Heart Association recommendations)

Group 2: CR (energy deficit 25%)

Group 3: CR 12.5% + PA 12.5% (energy deficit 25%)

Group 4: CR (LCD 800 kcal balanced liquid diet) followed after a 15% wt. reduction by wt. maintenance (“wt. clamping”).

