Subjects will be placed on an 800-kcal/d diet divided into 5 liquid portions (HEALTHONE). The diet will contain 70g of high quality protein, RDA of vitamins and minerals, 10g of fat with one meal and the remaining macronutrients as carbohydrate. Like the other 3 groups, subjects in this group will come to the metabolic kitchen every weekday to consume breakfast and dinner. The other liquid portions will be distributed daily to be consumed at home. Weekend meal replacements will be distributed Friday evening. Subjects will be seen in the clinic for measures of diet adherence, postural vital signs and metabolic weight once per week. Blood will be drawn and an electrocardiogram performed every 2 wks. If the chemistry panel shows potassium level below normal range, supplementation will be given. Upon achieving a 15% wt. loss, subjects will be progressively put back on solid food (same diet as other groups) in order to maintain the wt. loss. Subjects not attaining a 15% wt. loss by 14 wks. will be judged non-compliant and discharged**.**

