Individual tailoring of treatment. One aspect of lifestyle behavior modification, i.e. frequent and regular therapeutic contact, has been found to be very important for long-term behavior change. To accomplish frequent contact, treatment will be tailored to the needs of the individual participant using internet-based contact and/or telephone contact. Also, for persons who are having difficulty following the prescribed dietary or PA program, the intervention will be tailored to address the unique problems of the individual. The rate of predicted weight loss will be calculated using a 2-reservoir dynamic model of the energy balance equation as described by Alpert 128. This data will be used to monitor compliance and will not be shared with the volunteer. Metabolic weight will be measured once per week. Participants who fail to meet 60% of the expected rate of wt. loss will be interviewed very carefully to identify reasons for potential sup-optimal compliance with the prescribed treatment. Compliance will also be assessed by measures of metabolic rate, heart rate monitors, accelerometers and doubly labeled water. If problems related to compliance are identified, solutions to the problem will be established and individualized interventions will be initiated and tested for specified periods of time. If these interventions result in hypothesized changes in weight, they will be continued; if not, new strategies will be formulated and tested until success is achieved. Only after different tries, subjects will be asked to leave the study.

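### The only drop-out test fixed in the protocol is an all-group equality test, which does not isolate the CR+PA versus CR comparison that Hypothesis E makes, and its group count (3) conflicts with the four arms

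*Protocol*

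**What the plan says.** Hypothesis E (Hypotheses section) is a comparison of two arms: "Psychophysiologic outcomes are improved when the energy deficit is produced by combining PA and CR compared to CR alone". Its aims are to "Measure for differences in weight loss, compliance, rate of drop out, quality of life (QOL") and further measures. The background section on physical activity and quality of life gives the expected direction: the combined programme "would be associated with the lowest rate of attrition".

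The Power Calculation and Data Analysis section fixes one drop-out analysis: "The drop out rates will be compared across all treatment groups (3) testing for equality of proportions using the" chi-square test. It names no CR+PA versus CR contrast for drop-out and does not define drop-out.

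The Overall Description of the Experiment has the participants "divided into four equal groups matched for age and gender": control, CR, CR+PA and LCD.

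Participants can be made to leave under rules that differ by arm. For LCD, under Diets and diet delivery: "Subjects not attaining a 15% wt. loss by 14 wks. will be judged non-compliant and discharged". Under Timeline, participants who fall short of 60% of the expected rate of weight loss are interviewed and given individual interventions, and "Only after different tries, subjects will be asked to leave the study". Controls have no caloric restriction and so no weight-loss target to miss.

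**The concern.** The hypothesis concerns one pair of arms and has a direction. The test is non-directional and asks whether all groups share one drop-out rate. That null hypothesis can be false because of control or LCD, with CR and CR+PA the same. A real gap between CR and CR+PA can also be diluted by groups outside the hypothesis.

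Two ambiguities add to this. The stated count of three groups does not match the four arms, so a reader cannot tell whether LCD is in the test. Nor does the protocol say whether a mandated discharge counts as a drop-out. If LCD is in and discharges count, the LCD discharge rule alone can break equality.

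At stake is the conclusion on retention under Hypothesis E. Drop-out is not a primary endpoint and is not among the numbered secondary outcomes. The study does state feasibility and compliance as a purpose ahead of a longer trial, so a misread retention result would matter for planning.

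**Working it through.** **Plan's own figures.** The protocol gives no sample size, power or expected rate for the drop-out test, so there is no figure to reproduce. Table 2 does show how many groups the section was written for. Every total is 3 × n per group (for example 11 × 3 = 33). For the row with CV 5%, difference 10% and n = 11, take the SD of change as √2 × 5% = 7.07%, so d = 10/7.07 = 1.414. A one-way ANOVA with minimal variability of means has noncentrality n·d²/2 = 11 × 2/2 = 11. Power is 81.3% with three groups (80% printed) and 76.0% with four. The three-group assumption fits.

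**Inputs for the drop-out test.**
- n = 15 per arm: 60 participants in four equal groups, as also stated under Outcome measures. (The statistics section mentions 30 per group, which does not fit 60 in four groups.)
- Alpha 0.05, Pearson chi-square without continuity correction, df = groups − 1.
- Drop-out rates: none in the protocol. All rates and counts below are assumed.

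**Statistic.** With x leavers in each of k arms of 15 and pooled proportion p̄: X² = Σ(x − 15p̄)² / [15·p̄·(1 − p̄)].

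**Significant although CR equals CR+PA.**
- Four groups (control, CR, CR+PA, LCD), leavers 1, 1, 1, 6: p̄ = 9/60 = 0.15, expected 2.25 per arm. X² = (3 × 1.25² + 3.75²)/(15 × 0.15 × 0.85) = 18.75/1.9125 = 9.80, df 3, p = 0.020.
- Three groups (control, CR, CR+PA), leavers 0, 5, 5: X² = 6.43, df 2, p = 0.040.

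**Not significant although CR and CR+PA differ.** Fisher's exact test of 5 CR leavers against 0 CR+PA leavers gives p = 0.042.
- Four groups, leavers 2, 5, 0, 3: p̄ = 10/60, expected 2.5. X² = (0.25 + 6.25 + 6.25 + 0.25)/(15 × 1/6 × 5/6) = 13/2.083 = 6.24, df 3, p = 0.10.
- Three groups, leavers 3, 5, 0: p̄ = 8/45, expected 2.667. X² = (0.111 + 5.444 + 7.111)/(15 × 8/45 × 37/45) = 12.667/2.193 = 5.78, df 2, p = exp(−5.78/2) = 0.056.

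**How often the test rejects when CR and CR+PA have the same true rate** (exact enumeration of binomial outcomes, 15 per arm):

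| Groups tested | Assumed rates (%) | Rejects |
|---|---|---|
| Control/CR/CR+PA | 5/10/10 | 5% |
| Control/CR/CR+PA | 5/20/20 | 14% |
| Control/CR/CR+PA | 5/30/30 | 37% |
| Control/CR/CR+PA/LCD | 5/10/10/10 | 5% |
| Control/CR/CR+PA/LCD | 5/10/10/20 | 16% |
| Control/CR/CR+PA/LCD | 5/10/10/30 | 39% |
| Control/CR/CR+PA/LCD | 5/10/10/40 | 66% |
| All four equal | 10/10/10/10 | 4% |

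The last row shows that the test holds its level under its own null hypothesis. The fault is the question it answers.

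**Direct comparison, 15 versus 15.** The control and LCD rates no longer enter. Power is low: Fisher's exact test has 15% for 30% versus 10%, and 33% for 40% versus 10%. The uncorrected chi-square has 28% and 51%.

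**The case against.** The strongest reply is that the statistics section was written for three groups, most naturally control, CR and CR+PA. On that reading LCD is outside the test and its 14-week rule cannot affect the result. At 5/10/10% the test then rejects in 4.8% of trials, and leavers of 1, 1, 1 give p = 1.0. This stands, and it makes the LCD figures conditional. It does not rescue the test: control is still in it, and the three-group examples above go wrong in both directions.

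A second reply is that pairwise contrasts and the definition of drop-out are usual content of a statistical analysis plan, which is not at hand, and that the protocol does not exclude a follow-up test. That is fair for missing detail. Here, however, the protocol does choose a drop-out test, and the one chosen does not address the stated hypothesis. A follow-up made only after a significant overall result would miss cases such as 2, 5, 0, 3.

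Three stronger readings are tempting and not supported.
- A reader might infer that LCD discharges will drive the result. That needs LCD in the test, discharges counted as drop-outs, and high LCD rates that no section gives. The protocol expects up to 10 weeks to reach the loss and allows 14. With LCD at 10% or 15% the four-group test rejects in only 5% or 8% of trials.
- A reader might infer that Hypothesis E is about voluntary withdrawal only. Neither the hypothesis nor the background says so. Drop-out is listed beside compliance, and for a feasibility study total exits are arguably the more relevant figure. The removal rule under Timeline makes no distinction between CR and CR+PA.
- A reader might infer that retention is a headline result. It is absent from the numbered outcomes, and the protocol calls its secondary outcomes more descriptive.

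**Conclusion.** The concern holds in this form: drop-out is a Hypothesis E outcome for CR+PA versus CR, and the only drop-out test the protocol fixes does not isolate that contrast on either reading of the group count. The inconsistency between three and four groups is a plain error in the same sentence.

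The mismatch between hypothesis and test needs no assumption. Its size does: rejection with equal CR and CR+PA retention runs from the nominal 5% to 37% in the three-group cases shown, and from 5% to 66% in the four-group cases with control at 5% and CR and CR+PA at 10%. All of these use 15 per arm and assumed rates. The four-group figures, so far as LCD discharges raise the LCD rate, also assume that discharges count as drop-outs. The point is worth correcting but does not touch the primary endpoint.

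**What to change.** In Power Calculation and Data Analysis, replace the drop-out sentence so that it:
1. Names CR+PA versus CR as the Hypothesis E drop-out analysis, with all exits as the outcome, reported as a difference in proportions with an exact 95% confidence interval and Fisher's exact test.
2. Corrects the group count, states which groups any all-group comparison covers, and keeps that comparison descriptive.
3. Tabulates exits by arm and reason (participant withdrawal, protocol-mandated discharge, pregnancy or medical), with participant withdrawal alone as a supplementary analysis.

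The cost is a few lines of analysis wording and one reason-for-exit field completed when the participant leaves, since reasons are hard to reconstruct later. No discharge rule changes. The downside should be stated in the text: with 15 against 15, even 5 leavers versus 0 only just reaches p = 0.042, so the comparison is imprecise and should be presented as descriptive.
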